## 1. Introduction

The World Health Organization’s (WHO) Framework Convention on Tobacco Control (FCTC) suggests a number of measures to reduce the demand for and supply of tobacco. Elimination of all forms of illicit tobacco trade (Article 15) is an essential tobacco control measure [1,2]. Illicit trade may include large- and small-scale smuggling, illicit manufacturing, and counterfeiting of existing brands [1]. Cigarettes are a particularly attractive product to smugglers [2]. As cigarettes in Low- and Middle-Income Counties (LMICs) have relatively higher taxes compared to other tobacco products such as birris and smokeless tobacco [3], evading tax by diverting cigarettes into the illicit market (where sales are largely tax-free) can generate a considerable profit margin for smugglers [2,4]. Illicit trade undermines the effectiveness of tobacco tax policies, results in availability of cheap cigarettes to smokers, and thus increases tobacco use and tobacco related deaths [2,3]. Elimination or curbing illicit trade will therefore increase price and tax revenue to governments and reduce tobacco consumption and tobacco-related premature deaths [3,5].

The share of illicit in total cigarette consumption is estimated to be 11.6% globally and 16.8% in LMICs [2]. Tobacco companies claim that illicit trade in cigarettes has been growing rapidly since the 1990s [4], and often use inflated estimates of illicit cigarettes to argue against cigarette tax increases [5,6,7,8]. In the absence of national-level independent data on the extent of illicit cigarette trade and limited data on cigarette confiscation provided by the enforcement authorities [3,9], tobacco companies manipulate evidence to their advantage and use these tactics to continually lobby governments for reducing cigarette taxes [3,6,7].

In Bangladesh, 35.3% of adults (38 million) use tobacco regularly, 14% (15 million) use cigarette, and 5% (5.3 million) use “birri” [10]. However, there has been no independent published evidence measuring the extent of illicit tobacco trade in Bangladesh. Nevertheless, following industry estimates, it has been claimed that the illicit cigarette trade would be about 2% of the total cigarette market, leading to a revenue loss of 8 billion Taka, 4% of the total tobacco revenue [11]. 

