This protocol will present a mixed-methods study to estimate the extent of illicit cigarette trade in Bangladesh. Three research questions will be addressed: (a) What proportion of cigarettes sold as retail in Bangladesh are illicit? (b) What are the common types of tax avoidance and tax evasion in Bangladesh? (c) Can pack examination from trash recycle market be considered as a new method to assess illicit trade in comparison to that from retailers and streets? Findings from this study will help policy makers develop more effective tobacco control measures and refute industry claims in Bangladesh. 

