#### 2.2.1. Collecting Packs from Tobacco Retailers

The data collection team will determine a central point (such as a bus station, a government building, or a market place) in each PSU. All types of shops, such as tea stalls, kiosks, supermarkets, department stores, and cigarette shops that sell cigarettes or birri, or both, would be eligible to take part in the study. Enumerators will walk half a kilometer in both directions on the main street around the public gathering place and approach all the retailers meeting the eligibility criteria. All eligible retailers will be provided with both verbal and written information about the study. If they agree to take part, they will be required to sign the consent form. Following consent, the field worker will proceed to pack collection. The retailers would be supplied with a “collection bag” on the previous day and asked to keep all the empty packs resulted from loose sale on the following day since the shop opened in that bag. All “collection bags” will be retrieved by the field workers at the end of the business day. We will provide a small monetary reward of BDT 3 (GBP 0.03) per empty pack deposited in the collection bag. In case the empty pack of the cheapest and popular brands were not available in the bag from a particular retailer, the team would take a picture and code all the relevant attributes of such pack observed in the shop itself [3]. 

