In general, all pack characteristics considered for detecting legitimacy in the retailer sample might also be accepted for those in littered or trash samples. Nevertheless, one of the limitations of the above general approach is that it might fail to distinguish between tax evasion and avoidance. More specifically, there may be some legally purchased duty-free packs as well as those bought from neighboring countries, in a sample from street, while also having illegally purchased and illegally sold packs in the retail shops belonging to that street. This possibility might result in under- or overestimation of the illicit cigarette trade. Hence, it rationalizes the application of an adjustment factor while measuring the magnitude of illicit cigarette in the sample collected particularly from street and trash recycle market. Table 3 exemplifies a thematic presentation of legitimacy criterion of a cigarette pack and adjustment requirement in the estimation. 

Assuming that the littered packs in the streets would by and large reflect the average characteristics of those sold by different retailers on the same street, the following adjustment method would be applied:

Suppose DF_L_ is the proportion of duty-free packs (both legal and illegal) in the littered sample and DF_R_ is the proportion of duty-free packs (all illegal) in retailer sample. Then, the estimated proportion of illegal duty-free packs from littered sample would be
=DF_R_ if DF_L_ > DF_R_; and
=DF_L_ if DF_L_ ≤ DF_R_.   

Similar adjustment process would be followed while estimating extent of illicit cigarette using packs from trash recycle sample. It should be noted here that self-made cigarette using tax-paid tobacco powder or crushed tobacco may not be the scope of current work. However, a pack for a local category of cheap cigarette known as “birri” would be collected and examined for its compliance as per the study definition. Statistical Analysis (STATA) software version 15 would be used. The main statistical analysis will report the frequencies and proportions of cigarette packs that do not comply with the tobacco control laws and falls within the study definition of illicit. 

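### Read as written, birri packs enter the proportion that is meant for cigarettes, and brand-selected packs photographed in shops are not separated from the retailer sample

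*Protocol article*

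**What the plan says.** Research question (a), in section 1 of the protocol article, is: "What proportion of cigarettes sold as retail in Bangladesh are illicit". The same section says that cigarettes carry "relatively higher taxes compared to other tobacco products such as birris and smokeless tobacco", and it gives separate user counts of 15 million for cigarettes and 5.3 million for birri.

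Section 3 (Analysis Plan) describes birri differently, as a cheap local kind of cigarette whose packs "would be collected and examined for its compliance as per the study definition". Shortly afterwards it defines the output: "The main statistical analysis will report the frequencies and proportions of cigarette packs that do not comply with the tobacco control laws". The section keeps three databases, one for each pack source (retailers, streets, trash recycle market). It names no division by product.

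Section 2.2.1 admits all shop types, including "cigarette shops that sell cigarettes or birri, or both, would be eligible to take part in the study". The retailer bag holds the empties from one day's loose sales. If it contains no pack of the cheapest and popular brands, "the team would take a picture and code all the relevant attributes of such pack observed in the shop itself".

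Two other places bear on these photographed packs. Section 2.2.5 has packs inspected at the research office by data entry operators, who are trained with revenue officials in judging stamps. Section 4 excludes every pack whose stamp is not in a condition to be authenticated.

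**The concern.** There are two separate problems with what the retailer proportion measures.

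**Product.** Question (a) concerns cigarettes, and so does the industry-based figure of about 2% that the study hopes to test. If birri is a category of cigarette and is judged by the same illicit definition, its packs fall in the proportion of cigarette packs. If it is another product, as the Introduction has it, they do not belong there. The two sections give opposite answers.

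**Selection.** The bag is a sample generated by sales: a pack is in it because its cigarettes were sold loose that day. A photographed pack is added because its brand is cheap or popular and left no empty. It is also judged from what is seen in the shop, not by the trained office staff.

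The consequences go beyond the retailer estimate. The duty-free adjustment in section 3 caps the street share at the retailer share DF_R, and the trash sample is treated similarly, so a change in the retailer denominator can carry over to both. Section 4 takes the absence of systematic difference between sources as support for unbiasedness. Packs that exist only in the retailer sample can create or hide such a difference, which also affects question (c).

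**Working it through.** The article gives no pack count, expected proportion or precision on this point, so there is no figure of its own to reproduce. The check asks how far the proportion would move if the two groups were counted.

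**Inputs from the article (section 1).** Users: 15 million cigarette, 5.3 million birri. Two illustrative true proportions: 2.0% (industry-based, Bangladesh) and 16.8% (low- and middle-income countries).

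**Assumptions, none of them from the article.** Birri failure rate 2% to 50%; birri pack share 5% up to the share of users; 5 to 40 empties per shop; one or two photographed packs per shop (cheapest, popular); photographed-pack failure rate 0% to 30%.

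**Step 1, birri share of users.** 5.3 / (15 + 5.3) = 5.3 / 20.3 = 26.1%. This is a share of users, not packs, and the article does not say that the two user groups are exclusive. It serves only as an upper illustration.

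**Step 2, pooling birri.** Pooled = (1 − s) × p_cig + s × p_birri.

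| p_cig | s | p_birri | Pooled |
|---|---|---|---|
| 2.0% | any | 2% | 2.0% |
| 2.0% | 5% | 50% | 4.4% |
| 2.0% | 10% | 30% | 4.8% |
| 2.0% | 26.1% | 30% | 9.3% |
| 2.0% | 26.1% | 50% | 14.5% |
| 16.8% | 26.1% | 2% | 12.9% |
| 16.8% | 26.1% | 50% | 25.5% |

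For example, 0.739 × 2.0% + 0.261 × 50% = 14.5%. When the two failure rates are equal there is no shift. At 16.8% the shift can go either way.

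**Step 3, adding photographed packs.** Pooled = (m × p_bag + k × p_photo) / (m + k), with m empties and k photographed packs per shop.

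- True 2.0%, m = 5, k = 2: from 0.10 / 7 = 1.4% (none fail) to (0.10 + 0.60) / 7 = 10.0% (30% fail).
- True 2.0%, m = 20, k = 2: from 0.40 / 22 = 1.8% to (0.40 + 0.60) / 22 = 4.5%. These are the extremes for m of 20 or more.
- True 16.8%, m = 5, k = 2: from 0.84 / 7 = 12.0% to (0.84 + 0.60) / 7 = 20.6%.
- True 16.8%, m = 20, k = 2: from 3.36 / 22 = 15.3% to (3.36 + 0.60) / 22 = 18.0%.

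**Step 4, DF_R.** If none of the added packs is duty-free, two photographed packs per 20 empties multiply DF_R by 20 / 22 = 0.91. A birri share of 26.1% multiplies it by 0.739. Added packs that do carry a duty-free sign would work the other way.

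**Step 5, stamp inspection.** Section 2.2.1 has all relevant attributes of a photographed pack coded from what is seen in the shop. The training listed for data collectors in section 2.2.5 covers finding and handling packs, consent and bag identifiers; stamp authentication is taught to the office operators. The exclusion rule in section 4 would, on its face, remove a pack whose stamp cannot be authenticated, but its setting is empty packs. The three sections do not settle how a photographed pack is judged.

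**The case against.** The strongest reply is that no sentence puts either group into a denominator. Birri packs are said only to be collected and examined, the main analysis speaks of cigarette packs, and a separate birri table would fit that wording. A condensed article may leave tabulation to an analysis plan. Photographed packs may serve brand description: section 2.2.4 collects price and quantity for the same two brand types. The exclusion rule in section 4 might also remove those whose stamp cannot be checked.

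Part of this stands. Pooling is an inference, so a reader should not report it as a stated plan. But the point does not rest on a missing table. Section 3 itself classes birri as a cigarette and judges it by the definition that the main analysis uses, and the Introduction says otherwise. That contradiction is in the text.

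A reader might also infer that the estimate would be biased upward. The documents do not support that. They give no failure rate for birri or for photographed packs, and the Introduction ties the incentive to evade to the higher tax on cigarettes, which does not predict more evasion for birri.

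Nor should photographed packs be called unsold. The bag collects only empties from loose sales, so a brand sold that day in full packs leaves none. Section 4 concedes that full-pack sales may be missed, and it regards unopened packs as the better material for inspection. Leaving photographed packs out therefore does not make the retailer figure cover all cigarettes sold; it only keeps the sample to one selection mechanism.

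**Conclusion.** The point holds as a contradiction and an unsettled denominator, not as a demonstrated bias. The article is inconsistent on whether birri is a cigarette. Read as written, section 3 leads to birri packs being counted in the answer to a question about cigarettes. Photographed packs are selected by brand, confined to the retailer sample, and hard to square with the stamp inspection and exclusion rules.

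The direction of any shift is unknown, and every size above depends on assumed failure rates and pack shares. Within those assumptions birri matters more, because at a true proportion near 2% the choice of denominator could decide whether the study appears to support or refute the industry-based claim. The effect of photographed packs is modest once shops yield 20 or more empties, and larger where bags are nearly empty.

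**What to change.** 1. Reconcile sections 1 and 3 on whether birri is a cigarette or another tobacco product.
2. State that cigarette packs alone form the denominator for question (a), for DF_R, and for the comparison of retailer, street and trash samples. Report birri from each source in a separate table. Shops selling only birri can stay eligible and contribute to that table.
3. Flag photographed packs and keep them out of the main proportions, DF_R and the source comparisons. Use them for brand and price description, or in a labelled sensitivity analysis.
4. Reconcile sections 2.2.1, 2.2.5 and 4 on how the stamp of a photographed pack is judged and whether the exclusion rule applies to it.

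The cost is two flags in the databases, a few sentences, and slightly fewer packs in the main analysis. Fieldwork does not change.

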## Abstract

The illicit tobacco trade undermines the effectiveness of tobacco tax policies; increases the availability of cheap cigarettes, which, in turn, increases tobacco use and tobacco related deaths; and causes huge revenue losses to governments. There is limited evidence on the extent of illicit tobacco trade particularly cigarettes in Bangladesh. The paper presents the protocol for a mixed-methods study to estimate the extent of illicit cigarette trade in Bangladesh. The study will address three research questions: (a) What proportion of cigarettes sold as retail are illicit? (b) What are the common types of tax avoidance and tax evasion? (c) Can pack examination from the trash recycle market be considered as a new method to assess illicit trade in comparison to that from retailers and streets? Following an observational research method, data will be collected utilizing empty cigarette packs from three sources: (a) retailers; (b) streets; and (c) trash recycle market. In addition, a structured questionnaire will be used to collect information from retailers selling cigarettes. We will select post codes as Primary Sampling Unit (PSU) using a multi-stage random sampling technique. We will randomly select eight districts from eight divisions stratified by those with land border and non-land border; and within each district, we will randomly select ten postcodes, stratified by rural (five) and urban (five) PSU to ensure maximum geographical variation, leading to a total of eighty post codes from eight districts. The analysis will report the proportions of packs that do not comply with the study definition of illicit. Independent estimates of illicit tobacco are rare in low- and middle-income countries such as Bangladesh. Findings will inform efforts by revenue authorities and others to address the effects of illicit trade and counter tobacco industry claims.

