## 3. Analysis Plan

We will classify a cigarette pack as illicit if it has at least one of the following attributes: No mention of “retail price”: It is mandatory to print the retail price of the goods “on the body of the goods or on every package, sachets or cells distinctly, conspicuously and indelibly”. This applies to cigarettes, and packs not containing the retail price can be considered illegal [21].Mention of brand element: Packets should not contain any brand elements, for instance Light, Mild, Low Tar, Extra, and Ultra. Packs mentioning brand element will be considered illegal [22].No graphic health warnings: Health warnings shall be printed on both sides of the packet covering at least 50% of the total area of each main display area. In addition, the warnings should be in colored pictures. Rules notified further suggests that the ratio and written warnings should be 6:1 and the written warnings has to be printed in black background with white font color. Packs not fully complying the above rules will be considered illegal [21,22].No textual health warnings: The following warnings should be printed on the packet in Bengali, otherwise it can be considered as illegal [21,22].
(a)Smoking causes throat and lung cancer;(b)Smoking causes respiratory problems;(c)Smoking causes stroke;(d)Smoking causes heart disease;(e)Second-hand smoke causes harms to the fetus;(f)Smoking causes harms to the fetus; or(g)Second-hand smoking causes death.No declaration: Selling of tobacco products without having the statement “Sales allowed only in Bangladesh” printed on the packets would be illegal [22].A duty-free sign: Cigarette packs collected from retailers with a “duty-free” sign will be classified as illegal as these are to be sold in Duty Free shops only and should not be available in the market.Absence of correct and authentic tax stamp/banderole: The government has made it obligatory to use tax stamp or banderole on cigarette packets. Any sale of cigarette without this tax stamp or banderole is legally prohibited. The banderole/stamp of cigarette pack of different size and design had been defined [21]. We will check if the packs have used banderole/stamp correctly as per the SRO and VAT Booklet, and if the banderole/stamp is genuine.

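### Question (a) asks for the share of cigarettes sold, but the main analysis gives an unweighted share of packs; the two agree only if illicit and licit packs hold the same mean number of sticks

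*Protocol article*

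**What the plan says.** Research question (a), in the Introduction and again in the Abstract, is about cigarettes: "What proportion of cigarettes sold as retail in Bangladesh are illicit". Section 5 describes the aim in the same unit.

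The unit that is classified and reported is the pack. Section 3 begins "We will classify a cigarette pack as illicit if it has at least one of the following attributes" and fixes the main result as "The main statistical analysis will report the frequencies and proportions of cigarette packs that do not comply with the tobacco control laws". The Abstract agrees: "The analysis will report the proportions of packs that do not comply with the study definition of illicit".

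Three further statements bear on the point:

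- Under Section 2.2.1, retailers are asked to "keep all the empty packs resulted from loose sale on the following day". The retailer sample is therefore the residue of stick-by-stick sale.
- Section 3 says of the tax stamp: "The banderole/stamp of cigarette pack of different size and design had been defined".
- Section 3 adds a second product: "a pack for a local category of cheap cigarette known as “birri” would be collected and examined for its compliance".

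The article gives no number of sticks per pack, does not weight by sticks, and does not say that packs have equal content. The limitations in Sections 3 and 4 deal with duty-free packs, damaged stamps, selective deposit by retailers and full-pack sale. Pack content is not among them.

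**The concern.** The question and the main analysis use different units. In loose sale the customer buys sticks, and the empty pack is only a by-product. For the same number of sticks sold, a brand in packs of 10 leaves twice as many empties as a brand in packs of 20 (sizes chosen for illustration). A count of empties therefore gives more weight per cigarette to small packs.

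If illicit status goes along with pack content, the pack share is a biased answer to question (a), and collecting more packs does not reduce the bias. This matters because the study means to provide independent evidence against industry claims. The claim it cites is on a cigarette-market basis: "it has been claimed that the illicit cigarette trade would be about 2% of the total cigarette market". A pack share set beside that figure invites the objection that the units differ.

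**Working it through.** The article states no figure that could be reproduced for this point. The check is algebra, followed by a range.

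**Inputs**

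- Target: share of cigarettes (Introduction, question (a)).
- Reported quantity: share of packs, p (Abstract and Section 3).
- Illustrative values of p: 2% (the industry-based claim), 11.6% (global) and 16.8% (low- and middle-income countries), all from the Introduction. The article gives them as market or consumption shares. Here they serve only as plausible levels for p.
- r = mean sticks per illicit pack divided by mean sticks per licit pack, within one source. It is not in the documents, so it is an assumption: 0.8 to 1.25 as a moderate range, 0.5 and 2 as extremes.

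**Formula**

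Take N packs in one source, with mean content m_I for illicit and m_L for licit packs, so that r = m_I/m_L. Then

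stick share = pN·m_I / [pN·m_I + (1 − p)N·m_L] = pr / (pr + 1 − p).

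The difference from the pack share is p(1 − p)(r − 1) / (pr + 1 − p). For 0 < p < 1 it is zero only when r = 1. N cancels, so the difference does not depend on the number of packs.

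**Numbers**

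- p = 2%, r = 0.8: 0.016 / (0.016 + 0.98) = 0.016 / 0.996 = 1.61%.
- p = 2%, r = 1.25: 0.025 / (0.025 + 0.98) = 0.025 / 1.005 = 2.49%.
- p = 16.8%, r = 0.8: 0.1344 / (0.1344 + 0.832) = 0.1344 / 0.9664 = 13.91%.
- p = 16.8%, r = 1.25: 0.21 / (0.21 + 0.832) = 0.21 / 1.042 = 20.15%.

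| Pack share | r = 0.5 | r = 0.8 | r = 1 | r = 1.25 | r = 2 |
|---|---|---|---|---|---|
| 2% | 1.01% | 1.61% | 2.00% | 2.49% | 3.92% |
| 11.6% | 6.16% | 9.50% | 11.60% | 14.09% | 20.79% |
| 16.8% | 9.17% | 13.91% | 16.80% | 20.15% | 28.77% |

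**What does not cause an error**

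- Mixed pack sizes alone. If illicit and licit packs have the same mean content, r = 1 and the two shares coincide.
- A difference in size between sources alone. If every pack in one source held 20 sticks and every pack in another held 10, r would be 1 in each, and each pack share would equal its stick share.

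**The case against.** The best reply is that nothing in the article shows that r differs from 1. That is correct, and it limits the point in several ways.

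- A reader might take the stamp sentence in Section 3 as proof that pack content varies. The wording is ambiguous: size and design may belong to the stamp, which is the subject of that sentence. Even on the other reading it says nothing about content by licit status.
- A reader might suppose that illicit packs are mostly smuggled or duty-free and so differ in format. The study definition is much wider. Any one of seven attributes is enough, including a prohibited brand descriptor or a health warning that does not fully comply. Domestic packs with labelling faults can count as illicit, and these may have the same content as licit packs. That would pull r towards 1.
- A reader might infer that comparison across the three sources is distorted whenever pack sizes differ between them. The algebra does not support this. Only a difference between illicit and licit packs within a source matters.
- A reader might infer that pack content will not be recorded. Section 2.2.4 mentions a standard pack analysis tool whose fields are not shown, and it may well include it. That would make a stick-weighted estimate possible, but it does not alter the main analysis as written.
- No section commits to a numerical test against 2%, 11.6% or 16.8%. They are background figures.

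It can also be said that weighting is detail for the full protocol or analysis plan. An additional weighted estimate could indeed be specified there. But the article does not leave the main quantity open. It names the main analysis and its unit, and that unit is not the one in question (a). This part of the point stands. Stick weighting would not repair the omission of full-pack sales from the retailer sample, which Section 4 already acknowledges; that is a separate limitation.

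**Conclusion.** The mismatch is in the text: question (a) is about cigarettes, and the main analysis reports an unweighted proportion of packs. The second answers the first only if illicit and licit packs within a source hold the same mean number of sticks, and the article neither states nor assumes this.

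The consequence is conditional. With no stick counts by licit status, neither direction nor size can be fixed, and the documents do not support saying that the result will be biased, or in which direction. Under the assumed moderate range, the shift is about 0.4 to 0.5 percentage points at a pack share of 2% and about 3 points at 16.8%. The columns for r = 0.5 and r = 2 are outer limits chosen for illustration and should not be read as expected values.

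The point does not invalidate the design. It should be settled before analysis, because the remedy is cheap and serves the study's own first question.

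**What to change.** 1. Record the stated number of sticks on each pack during the inspection at the research office (Section 2.2.5), if the pack analysis tool does not already do so.
2. Answer question (a) with the stick-weighted share, separately for each source, and report the pack share beside it.
3. Report birri separately, so that its packs are not pooled with cigarette packs in one denominator.
4. Compute DF_L and DF_R in Section 3 as shares of sticks. The duty-free adjustment is a cap at group level. When it applies, nobody knows which individual littered packs are illegal, so their sticks cannot simply be summed; with both terms in sticks, the rule carries over unchanged.
5. Packs are empty and some will be damaged. Where the number cannot be read, assign a count by brand or pack format, and report how many packs were handled in this way.

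The cost is one field on packs that are inspected individually anyway, and a weight in the analysis. The downsides are slightly wider intervals and some imputed counts.

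If sticks cannot be recorded, question (a) and the conclusion should be restated as a proportion of packs, and any comparison with shares of the cigarette market should note the difference in unit.
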